**Storyline Health Assessments:**

- Patients will be notified through the Storyline app on their smartphone or smart device to complete the various study assessments. Storyline manages reminders and makes the process simple.

## Storyline Integrative Assessment - Neurological, Psychiatric, Cognitive and Psychological

© Copyright Storyline Health 2022

**Summary:**

This 25-minute assessment enables deep, objective profiling of neurological, psychiatric, cognitive and psychological phenotypes and symptoms using artificial intelligence. Patients perform the interactive video interviews and questionnaires on their smartphone and their responses are video recorded and stored in the cloud in the HIPAA, GDPR and HiTech compliant Storyline Vault, which provides state-of-the-art military grade security and is specialized for health data privacy. The video and audio data is analyzed by Storyline AI algorithms that measure >20,000 facial, vocal and speech micro-expressions to monitor symptoms and discover biomarkers and predictive models. Applications include drug treatment studies, basic research of brain functions and health, monitoring wellbeing, biomarker discovery, predictive model discovery, assessment discovery, disease modeling and precision medicine applications. See Appendix 1.

- The Data Monitoring section outlines how participant data is collected, stored and managed through the Storyline Health platform. Participants are owners of their data and can access it at any time, and even delete it. However, the study will not be able to provide direct meaningful interpretations for participants. Note, that participants may be able to choose some non-research interactions within the Storyline app, such as what celebrities they look like. This is not considered a benefit nor will be included in the research data, it’s for entertainment purposes for the participants. Please see section 15.4 on **Storyline Health Data Confidentiality and Security.**
  1. Toronto Mindfulness Scale (TMS), Five-Facet Mindfulness Questionnaire (FFMQ), CERQ Positive Reappraisal Questionnaire.

**Trait Mindfulness** will be measured the Five Facet Mindfulness Questionnaire (FFMQ), with higher scores indicating greater trait mindfulness. **State Mindfulness** will be measured the Toronto Mindfulness Scale (TMS), with higher scores indicating greater state mindfulness. **Reappraisal** will be measured via the positive reappraisal subscale of the Cognitive Emotion Regulation Questionnaire (CERQ), with higher scores indicating more frequent use of reappraisal. These measures will be used to ascertain whether PAP augments therapeutic mechanisms known to be targeted by MBSR.

Effects of MBSR+PAP vs MBSR on these outcomes will be evaluated using GLMMs similar to those used to examine depression and burnout. Fixed effects consist of a time factor and between-subjects treatment factors. Our primary interest lies in the Treatment X Time interaction, expressible as a linear contrast on the β parameters. Repeated effects will incorporate additional dependence, if needed and supported by the Bayesian Information Criterion (BIC), in the form of autoregressive of the linear predictor.

- 1. Path analysis will assess changes in the Mystical Experience Questionnaire (MEQ-30), Challenging Experience Questionnaire, Nondual Awareness Dimensional Assessment (NADA)- both state and trait versions, and Brief Savoring Inventory (BSI) as mediators of the effect of MBSR+PAP on burnout, using bootstrapping to assess the significance of the indirect effect (Preacher & Hayes, 2008). These will be summarized with descriptive statistics, including mean, median, range, standard deviation, and 95% confidence intervals.

# REGISTRATION GUIDELINES

Study-related screening procedures can only begin once the subject has signed a consent form. Patients must meet all of the eligibility requirements listed in Section 5 prior to registration. Patients must be registered before receiving any study treatment and must begin treatment as soon a logistically possible after registration.

# DATA SUBMISSION SCHEDULE

The Case Report Forms (CRFs) are a set of (electronic or paper) forms for each subject that provides a record of the data generated according to the protocol. CRFs should be created prior to the study being initiated and updated (if applicable) when amendments to the protocol are IRB approved. These forms will be completed on an on-going basis during the study. The medical records will be a source of verification of the data. During the study, the CRFs will be monitored for completeness, accuracy, legibility, and attention to detail by a member of the Research Compliance Office. The CRFs will be completed by the Investigator or a member of the study team as listed on the Delegation of Duties Log. The data will be reviewed no less than annually by the Data and Safety Monitoring Committee. The Investigator will allow the Data and Safety Monitoring Committee or Research Compliance Office personnel access to the subject source documents, clinical supplies dispensing and storage area, and study documentation for the above-mentioned purpose. The Investigator further agrees to assist the site visitors in their activities.

**Data capture should be restricted to endpoints and relevant subject information required for planned manuscripts.**

# ETHICAL AND REGULATORY CONSIDERATIONS

## Human Subject Protections

The study will be conducted in accordance with the appropriate FDA, IRB, ICH GCP, and other federal and local regulatory requirements, as applicable. Informed consent will be obtained from all research participants prior to performing any study procedures using the most recent IRB-approved version. All patients must be at least 18 years of age to participate.

## Institutional Review

Before study initiation, the investigator must have written and dated approval/favorable opinion from the IRB/IEC for the protocol, consent form, subject recruitment materials (e.g., advertisements), and any other applicable subject-facing documents. The investigator should also provide the IRB/IEC with a copy of the Investigator Brochure or product labeling information.

The investigator or designee should provide the IRB/IEC with reports, updates and other information (e.g., expedited safety reports, amendments, and administrative letters) according to regulatory requirements or institution procedures.

## Data and Safety Monitoring Plan (see DSMB protocol)

A Data and Safety Monitoring Board (DSMB) will be established by our team consisting of multiple stakeholders to ensure the well-being of patients enrolled on Investigator Initiated Trials that do not have an outside monitoring review. We intend to follow the roles and responsibilities of the DSMC are set forth in the NCI-approved Data and Safety Monitoring (DSM) plan. The activities of the committee include reviewing adverse events (including SAEs), deviations, important medical events, significant revisions or amendments to the protocol, reviewing CRFs, and approving cohort/dose escalations. If the DSMB and/or the PI have concerns about unexpected safety issues, the study will be stopped and will not be resumed until the issues are resolved.

This study is classified as high risk per the NCI-approved DSM plan.  The IRB and DSMB will be notified of all serious adverse events (SAEs).  All serious events will be reviewed by the full DSMB monthly.

**DSMB** **members**

**(chair) [name] [name] PhD** (Associate Professor of Psychiatry, University of Utah) is a board-certified Psychiatrist and researcher.

**[name] PhD (Assistant Professor of Psychiatry, University of Utah) is a board certified psychiatrist, researcher, and bioethicist.**

**[name]** (Assistant Professor of Emergency Medicine and Palliative Medicine, University of Utah) is board certified in Emergency Medicine and Hospice and Palliative Medicine.

**[name]** (Counseling Psychology Doctoral Candidate, University of Utah) is a PhD candidate in Counseling Psychology.

**[name]** (Assistant Professor of Psychiatry, University of Utah) is a board-certified psychiatrist.

Serious adverse events include life-threatening cardiac arrhythmias, respiratory arrest, myocardial infarction, stroke, destabilizing psychiatric event such as sustained psychosis and death.

The most common adverse events associated with psilocybin are mild or moderate in severity and include dysphoria, anxiety or panic attacks, negative emotional states, paranoid/delusional thinking during dosing sessions along with increased blood pressure (BP) heart rate, mild nausea and mild headache. These will be discussed with the DMSB quarterly as the study progresses.

Each participant will be monitored at least 3 times the week before and after psilocybin dosing to assess for any adverse events, including C-SRSS testing and vital sign monitoring.

*Participants will be withdrawn if:* 
1. They experience an unexpected or serious adverse event 
2. Depression or suicidal ideation worsens and a higher level of psychiatric care is needed at the discretion of the PI

3.The study team discovers any new information placing the participant at excessive risk if they continue in the study

*The Data and Safety Monitoring Board will be informed of:* 
1. Adverse events, whether expected or unexpected 
2. Study progress: number of participants enrolled, randomized, completed

There will be monthly monitoring by the study team and a formal review by the DSMB quarterly for the duration of the study.

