# OBJECTIVES

## Primary Objectives

### Determine the acceptability, feasibility, and safety of psilocybin-assisted therapy (PAP) plus Mindfulness-Based Stress Reduction (MBSR) for front-line healthcare worker burnout.

*Primary Endpoint:* Acceptability of each modality will be determined by ease of enrollment and retention. Feasibility will be measured by the number of enrollees who successfully complete each modality in both study arms. Safety will be measured through the monitoring of adverse events (AEs) utilizing the CTCAE (NCI Common Terminology Criteria for Adverse Events Version 5.0), suicidal ideation utilizing the Columbia Suicide Severity Rating Scale (C-SSRS), administration of the Challenging Experiences Questionnaire (ChEQ), direct participant qualitative reports, and clinician observation.

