#### The Psilocybin Session

The psilocybin medication session will occur in a group space in HMHI. This space will have accessibility to a restroom, a private break-out room (to be used as needed), and the HMHI pharmacy. Code Blue response is available within the facility. There will be a 1:1 ratio of therapists to participants present as well as a lead therapist not specifically assigned to any one participant. The room will have a chair for the individual therapists to sit near the subject to offer support and guidance. Participants will be seated in individual “stations” but will be within visual and auditory reach of those in their cohort. There will be a more private space available if the lead therapist and individual therapist deem an individual as needing it, mostly in a scenario in which loud speaking, crying or other behavior becomes disruptive to the group. Video recording equipment will be present throughout the duration of the session and will be part of the consenting process. Participants will be given specific reminders regarding the process for using the restroom or having a light snack. Participants will remain on-site with their therapist team for eight hours after administration of psilocybin and will have arranged transportation from the study site at the end of the day.

Prior to leaving the site at the end of the psilocybin dosing day each participant will be assessed by the lead study monitor ([name] MD or [name] MD) regarding safety to leave. This evaluation will consist of a medical screen for any concerning symptoms, a psychiatric screen for acute suicidality or significant emotional distress, and a cognitive screen assessing orientation. If there are clinical concerns that a given participant is not safe to leave the site along medical, psychiatric, or cognitive assessments the lead study monitor (one of the PIs) and the Lead Therapist will remain on site for ongoing assessment and support until the participant is deemed safe to depart with a designated ride and support person. If a given participant remains unsafe to leave the site despite ongoing assessment and support they will be escorted to either the HMHI Receiving Center (for psychiatric assessment and care) or the University of Utah Emergency Department depending on either psychiatric or medical clinical presentation.

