#### Integration Sessions

Three group integration sessions will occur after the Psilocybin Session with the first occurring within 48 hours of the Psilocybin Session. Integration sessions will be 90 minutes in duration and participants may join up to two of these sessions remotely via Zoom at the clinical judgement of the study therapists and study team if there are scheduling difficulties. This material will also be buttressed by specific integration exercises through the Storyline platform. Focus of these sessions includes processing material that arose during the psilocybin session, examining emotional responses to this material, review of significance of this material in light of symptoms of depression and burnout, reflection on how to integrate this material into the workplace and personal life following the psilocybin session, practices to continue integrating this experience moving forward.

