**Table 2: Schedule of Events**

| **Week** | **-5 to -1** | | **1** | **2** | **3** | **4** | **5** | **6** | **7** | **8** | **9** | **11** | **33** |
| --- | --- | --- | --- | --- | --- | --- | --- | --- | --- | --- | --- | --- | --- |
| **Day** | **-35 to -7** | | **0-7** | **8-14** | **15-21** | **Etc.** |  |  |  |  |  |  |  |
| **Study Stage** | **Screen** | | **Active** | | | | | | | | | **Follow-up^[[1]](#endnote-1)^** | |
| Informed consent, registration | x |  |  |  |  |  |  |  |  |  |  |  |  |
| Eligibility criteria | x |  |  |  |  |  |  |  |  |  |  |  |  |
| Demographics | x |  |  |  |  |  |  |  |  |  |  |  |  |
| Medical History | x |  |  |  |  |  |  |  |  |  |  |  |  |
| Vitals and PE^[[2]](#endnote-2)^ | x |  |  |  |  |  |  |  |  |  |  |  |  |
| Randomization/assignment | **x** |  |  |  |  |  |  |  |  |  |  |  |  |
| Expectancy Questionnaires |  | **x** | **x** |  |  |  |  |  |  |  |  |  |  |
| **MBSR ARM** |  |  | **1** | **2** | **3** | **4** | **5** | **6** | **7** | **8** | **9** | **11** | **33** |
| **MBSR course** |  |  | **x** | **x** | **x** | **x** | **x** | **x** | **x** | **x** |  |  |  |
| **Retreat** |  |  |  |  |  |  |  |  | **x** |  |  |  |  |
|  |  |  |  |  |  |  |  |  |  |  |  |  |  |
| **PAP-MBSR** |  |  | **1** | **2** | **3** | **4** | **5** | **6** | **7** | **8** | **9** | **11** | **33** |
| Comprehensive Metabolic Panel ^xi.^ |  | x |  |  |  |  |  |  |  |  |  |  |  |
| Urine drug screen |  | **x** |  |  |  |  |  | x (within 24 hrs) |  |  |  |  |  |
| Pregnancy test ^iii^ |  | x |  |  |  |  |  | x (within 8 days of PAP) |  |  |  |  |  |
| MBSR Course |  |  | **x** | **x** | **x** | **x** | **x** | x | x | **x** |  |  |  |
| Prep Sessions 1-3 |  |  |  |  |  |  | **x** | x |  |  |  |  |  |
| PAP Session |  |  |  |  |  |  |  |  | x |  |  |  |  |
| Vitals monitoring |  |  |  |  |  |  |  |  | **x^[[3]](#endnote-3)^** |  |  |  |  |
| Integration Sessions 1-3 |  |  |  |  |  |  |  |  | **x** | **x** | **x** |  |  |
| **Assessments** |  |  | **1^[[4]](#endnote-4)^** | **2** | **3** | **4** | **5** | **6** | **7** | **8^[[5]](#endnote-5)^** | **9** | **11** | **33** |
| PHQ-9 | x |  |  |  |  |  |  |  |  |  |  |  |  |
| MBI-HSS (MP) | x |  | x |  |  |  |  |  |  |  |  | x | **x** |
| QIDS-SR-16 |  |  | x |  |  |  |  |  |  |  |  | x | **x** |
| Demoralization II scale |  |  | x |  |  |  |  |  |  |  |  | x |  |
| PTSD Checklist 5 |  |  | x |  |  |  |  |  |  |  |  | x | **x** |
| MEQ-30 |  |  |  |  |  |  |  |  | x |  |  |  |  |

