| Challenging Experience Questionnaire |  |  |  |  |  |  |  |  | x |  |  |  |  |
| Nondual Awareness Dimensional Assessment (state) |  |  |  |  |  |  |  |  | x | **x** |  |  |  |
| Nondual Awareness Dimensional Assessment (trait) |  |  | **x** |  |  |  |  |  |  |  |  | **x** |  |
| Watts’ Connectedness Scale |  |  | x |  |  |  |  |  |  |  |  | x | **x** |
| Toronto Mindfulness Scale, FFMQ-15 |  |  | x |  |  |  |  |  |  |  |  | x | **x** |
| Brief Savoring Inventory |  |  | x |  |  |  |  |  |  |  |  | x |  |
| **Storyline Health Questionnaires** |  |  |  |  |  |  |  |  |  |  |  |  |  |
| **Storyline Integrative Assessment**: Neurological, Psychiatric, Cognitive, Psychological |  |  | x |  |  |  |  |  |  |  |  | x | **x** |
| Qualitative assessment on workplace functionality ^vii.^ |  |  | x |  |  |  |  |  |  |  |  | x |  |
| Qualitative assessment on relationship between mindfulness training and psilocybin session and group format ^x^ |  |  |  |  |  |  |  | **x** |  |  |  | x |  |
| **Safety** |  |  |  |  |  |  |  |  |  |  |  |  |  |
| CTCAE Adverse Event collection^[[6]](#endnote-6)^ | x |  | x |  | x |  | x | x | x | x | x | x | **x** |
| Assess suicidality: C-SSRS ^x^ | x |  |  |  |  |  |  | x |  | x | x | **x** | **x** |
| Assess concomitant meds | x |  | x |  | x |  | x | x | x | x | x | x | **x** |

^i.^ Follow up measures to be administered 14 days (+/- 3) and 180 days (+/-7) after final MBSR session in week 8.

^ii.^ Vital signs include systolic and diastolic blood pressure, heart rate, respiratory rate, pulse oximetry, weight. Weight captured at screening only.

^iii.^ Pregnancy test (serum or urine) must be obtained at screening and ≤ 8 days prior to psilocybin administration for all women of childbearing potential and as clinically indicated while on trial.

^iv.^ On day of psilocybin administration vital signs will be assessed approx. 10 min before dosing and at 30, 50, 90, 120, 180, 240, 300, and 360 minutes after psilocybin administration. The baseline vitals will be allowed a 60-minute window to collect prior to dosing, while each subsequent vital collection will be allowed a window of +/- 15 minutes.

^v.^ All Questionnaires scheduled for MBSR Week 1 to be administered prior to the first MBSR session. Questionnaires and safety measures assessed similarly across both study arms.

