^vi.^ Integration sessions #1 and #2 both included in this week for the PAP + MBSR arm. Adverse event collection, suicidality, concomitant meds will all be assessed x 2 during this week for the PAP+MBSR arm.

^vii.^ This will consist of a 3-minute free-form video recorded response on the Storyline platform by participants regarding perceived functioning in the workplace.

^viii.^ This will consist of a 3-minute free-form video recorded response on the Storyline platform by participants regarding perceived reciprocal effects of mindfulness training and psilocybin session.

^ix.^ Adverse event collection will occur during all 3 preparatory sessions and all 3 integration sessions for the PAP+MBSR arm. Adverse event monitoring can occur via phone contact for intervals prior to psilocybin dosing.

^x.^ If subject is rated as moderate or high risk a full C-SSRS will be completed.

^xi.^ A comprehensive metabolic panel will be done by ARUP laboratories and will be done before the start of MBSR curriculum.

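### Table 2 schedules no C-SSRS in dosing week 7, and conflicting visit anchors leave open whether the 28-day post-dose ideation monitoring is covered

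*Protocol*

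**What the plan says.** **The instrument and the window.** Section 1.1 names the C-SSRS as the measure of suicidal ideation within the primary safety endpoint. Sections 9.4, 11.3 and 15.5 each state that participants are monitored for suicidal ideation for 28 days after psilocybin. Section 10.4 says this is done at the time points in the Schedule of Events, and Section 8 says that schedule applies for the entire study.

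**Table 2.** The psilocybin session is in week 7. The row "Assess suicidality: C-SSRS" is marked at screening and in weeks 6, 8, 9, 11 and 33; the week-7 cell is blank. The row "Integration Sessions 1-3" is marked in weeks 7, 8 and 9. Footnote vi, attached to week 8, says "Integration sessions #1 and #2 both included in this week for the PAP + MBSR arm" and has suicidality assessed twice in that week.

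**Session 1.** Section 6.1 says "Three group integration sessions will occur after the Psilocybin Session with the first occurring within 48 hours of the Psilocybin Session".

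**Dosing day.** Section 6.1 requires, before departure, "a psychiatric screen for acute suicidality or significant emotional distress". Sections 9.4 and 10.4 repeat the requirement. None of the three names an instrument.

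**Follow-up anchor.** Footnote i says "Follow up measures to be administered 14 days (+/- 3) and 180 days (+/-7) after final MBSR session in week 8". The column it governs is labelled week 11. Section 9.4 counts the two weeks from the end of the group sessions, and Section 6.4 gives the psilocybin arm a ninth week for an integration session after the MBSR course ends.

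**Monitoring plan.** Section 15.3 (DSMB members) says "Each participant will be monitored at least 3 times the week before and after psilocybin dosing to assess for any adverse events, including C-SRSS testing"; it also lists vital signs.

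**The concern.** Three parts of the protocol describe suicidality checks around the dose, and they do not agree. A team that follows Table 2, as Sections 8 and 10.4 direct, could hold the first post-dose session without a C-SSRS. It could also make its last C-SSRS before the six-month visit some days short of day 28.

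Participants have a depressive disorder, and Section 15.3 classes the study as high risk. It also makes worsening suicidal ideation that needs a higher level of care a ground for withdrawal, so detection affects how an individual is managed. Section 15.5 ends adverse event collection at day 14 but extends suicidality monitoring to day 28, which suggests that the later part of the window was meant to have its own checks.

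**Working it through.** No sample size, power or error rate is involved. The check is a count of table cells and day arithmetic.

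**Day grid.** From week 2 on, Table 2's weeks run from day 7n − 6 to day 7n. Week 7 is days 43–49, week 8 is 50–56, week 9 is 57–63, week 10 is 64–70 and week 11 is 71–77.

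**1. Where session 1 falls.** With dosing on day d, session 1 is due by d + 2.
- It is certain to be in week 7 if d + 2 ≤ 49, that is, dosing on days 43–47.
- It can fall in week 8, as footnote vi assumes, only if dosing is on day 48 or 49.
- The integration row's week-7 mark fits the first case and contradicts the footnote. In that case the C-SSRS row offers nothing until week 8.

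**2. The last C-SSRS before the 180-day visit.** Let x be the days from dosing to the week-8 class.

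Footnote i puts the visit at x + 14, with a window of ±3:
- Dosing on the class-7 day, x = 7: 7 + 14 = day 21, window 18–24.
- Dosing strictly between weekly classes 6 and 7 (the retreat slot in Section 4.1), x = 8 to 13: nominal day 22–27, window 8 + 11 = 19 to 13 + 17 = 30.
- Day 28 is reached nominally only if x ≥ 14. With the full +3 it is reached if x + 17 ≥ 28, that is, x ≥ 11.
- Section 6.1 lets dosing move by a week either way. From x = 7, that gives x = 0, 7 or 14, so nominal day 14, 21 or 28. Early dosing can reach day 28; late dosing widens the shortfall.

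Section 9.4's anchor, assuming integration session 3 is 7 days after class 8, puts the visit at x + 7 + 14 = x + 21:
- x = 7: day 28.
- x = 8 to 13: day 29–34.

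The column label agrees with Section 9.4 and not with footnote i:
- Footnote i: days 50–56 plus 14 = days 64–70, which is week 10.
- Section 9.4: days 57–63 plus 14 = days 71–77, which is week 11.
- From week 7 to week 11 on the same weekday is 28 days. Across all days of those two weeks it is 71 − 49 = 22 to 77 − 43 = 34.

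**3. Section 15.3 against Table 2.**

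| | Week 6 | Week 7 | Week 8 |
| --- | --- | --- | --- |
| C-SSRS in Table 2, psilocybin arm | 1 | 0 | 2 |
| Vital signs in Table 2 | none | dosing day | none |

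Read per week, Section 15.3 asks for at least 3 before and 3 after, against 1 and at most 2 scheduled. Pooled over the two weeks, 1 + 2 = 3 meets it for the C-SSRS. For vital signs, Table 2 has only screening and dosing day.

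**The case against.** **Participants are not left unwatched.** A suicidality screen is mandatory before anyone leaves on dosing day. Therapists are reachable by phone until session 1. Adverse events are collected in week 7 and at every integration session. Footnote vi, taken alone, attaches a suicidality check to session 1. All of this stands. It limits the week-7 point to the missing structured instrument, in the case where session 1 falls in week 7.

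**The 28-day text names no instrument and no closing check on day 28.** That is true. A C-SSRS at dose + 28 days is therefore a recommended way to cover the window, and no wording in the protocol requires it.

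**The visit may well fall late enough.** The week-11 label, Section 9.4 and the primary analysis text in Section 12.2 (two weeks after the full protocol is completed, in both arms) point to the later date. Several secondary endpoints in Section 1.2 count from the end of MBSR, as footnote i does. A reader might infer that the protocol breaks its 28-day undertaking, or that no C-SSRS follows day 28. The documents support neither: the date depends on which anchor is used, early dosing or the +3 limit can reach day 28, and a C-SSRS is marked at week 33.

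**Adverse event collection may not stop at day 14.** Section 10.2 collects events from enrolment to study termination, Section 12.2 says much the same, and Table 2 marks contacts in weeks 9 and 11. So it would be too strong to say that the C-SSRS is the only safety contact late in the window.

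**Section 15.3 may be meant loosely.** A pooled count removes the C-SSRS mismatch. A flat contradiction on that count cannot be claimed; the mismatch on vital signs remains. The per-week reading would supply an early C-SSRS, but Section 10.4 sends staff to Table 2, where it does not appear.

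**Conclusion.** The point holds as a modest correction to the safety schedule. Week 7 has no scheduled C-SSRS, and with dosing on days 43–47 the session due within 48 hours falls in that week, preceded only by a dosing-day screen with no named instrument. Under footnote i the last C-SSRS before the 180-day visit is nominally 28 − 27 = 1 to 28 − 21 = 7 days short of day 28, for dosing from just after class 6 up to the class-7 day. Under the other anchor it is at about day 28 or later. The protocol therefore does not fix whether its 28-day monitoring is covered. Section 15.3 needs one stated meaning.

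The consequences are limited. Suicide attempts, serious adverse events (to day 28) and other adverse events are captured separately, and ideation is not a stopping trigger. No efficacy estimate or decision rule changes.

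The figures assume weekly classes, Table 2's own day grid, and integration session 3 one week after class 8.

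**What to change.** - Attach a C-SSRS to the integration session held within 48 hours of dosing, in whichever week it falls, and make footnote vi and the integration row agree.
- Add a C-SSRS at dose + 28 days, by phone or telemedicine as Section 10.4 allows, and complete it for the first cohort before accrual reopens after the hold in Section 4.1.
- Give the two-week follow-up visit one anchor, used in footnote i, the column label and Section 9.4.
- Restate Section 15.3 with a single C-SSRS frequency that matches Table 2, and limit vital signs to dosing day unless in-person checks on other days are intended.

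**Cost.** One amendment to the table and its footnotes, with matching wording in Sections 9.4 and 15.3. The dose + 28 check adds 1 screen; the session-1 check adds 0 if a week-8 check is moved, or 1 if it is new. That is 1 to 2 short screens per psilocybin participant, or 12 to 24 for 12 participants, by existing staff.

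Adopting Section 15.3 in full on the per-week reading would cost more: at least (3 − 1) + (3 − 2) = 3 extra C-SSRS screens and up to 3 + 3 = 6 in-person vital-sign checks per participant, the latter up to 6 × 12 = 72 in total.
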